### B-mode US

For each participant, B-mode US examination was performed using a US system (RS 85, Samsung Medison, Co. Ltd.) with a convex probe (CA1-7A). All participants were requested to fast for at least 8 h before the US examinations. Hepatic steatosis will be graded subjectively by the operator as no steatosis, mild steatosis, moderate steatosis, severe steatosis. They were be graded based on the following findings: (1) higher echogenicity of the liver, (2) impaired visualization of the intrahepatic vessels, and (3) impaired visualization of the diaphragm and posterior right hepatic lobe due to ultrasound beam attenuation (21).

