### QUS techniques

The QUS technique was utilized to evaluate each participant in this study. A US system with a convex probe was used to conduct the QUS analysis (RS 85, Samsung Medison, Co. Ltd.). Two QUS parameters, namely AC-TAI and SC-TSI, were calculated from the RF data using an inhouse program developed in MATLAB R2015a (MathWorks, Inc.). The color-coded maps of both AC-TAI and SC-TSI were produced by analyzing the RF data of the corresponding B-mode images.

To determine the TAI and TSI maps of the liver parenchyma, one researcher carefully placed ROIs (approximately 2 cm in inner arc length and 4 cm in height) on the B-mode images while avoiding large vessels, focal lesions, and reverberation artifacts under the liver capsule. In cases where blood vessels were unavoidable, the areas containing large vessels were excluded from the calculation of AC-TAI and SC-TSI, which resulted in vacant regions on the TAI and TSI maps. The MRI-PDFF results were unknown to the researchers when measuring the QUS parameters. The five measurements for each examination were averaged for each QUS parameter.

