### Sample size

To ensure accurate evaluation of QUS techniques for hepatic steatosis grading, it is imperative to calculate the required sample size. Assuming an 80% MAFLD prevalence in the target population and 80% sensitivity and 90% specificity in QUS techniques, we calculated the minimum number of subjects needed to be 75 using a paired non-parametric test in the non-parametric module of PASS. Considering factors like data loss, cases “lost to follow-up”, our study will involve 100 patients scheduled to undergo RYGB.

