### Data analysis

The statistical analysis for this study will be performed using the SAS 9.2 software package (SAS Analytics, Marlow, UK) and R (v4.3.1; R Core Team), which is widely available for commercial use. The significance level has been predetermined to be 0.05 for all two-sided tests. The mean and standard deviation will be used to express normally distributed quantitative data.

To compare quantitative data, a paired t-test will be employed. Meanwhile, categorical variables will be analyzed using the chi-squared test. Pearson correlation coefficients will be utilized to evaluate the relationship between QUS parameters and other factors under consideration. Univariable linear regressions of QUS and other methods on MRI-PDFF were conducted to calculate the adjusted linear correlation coefficient (r). Then receiver operating characteristic (ROC) curves of QUS and other methods for the detection of MRI-PDFF ≥5% and ≥10% were plotted. The best cut-off values were defined as the cut-off values corresponding to the maximum Youden indexes.

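### Cut-offs set at the maximum Youden index, with no validation or correction described, overstate sensitivity plus specificity for every continuous method and distort any cut-off-based comparison

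*Protocol article*

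**What the plan says.** The Data analysis section plans that "receiver operating characteristic (ROC) curves of QUS and other methods for the detection of MRI-PDFF ≥5% and ≥10% were plotted". It then fixes how a cut-off is picked: "The best cut-off values were defined as the cut-off values corresponding to the maximum Youden indexes". The same rule covers QUS and its comparators.

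The scales differ. For B-mode, "Hepatic steatosis will be graded subjectively by the operator as no steatosis, mild steatosis, moderate steatosis, severe steatosis", which leaves three possible cut-points. AC-TAI and SC-TSI are continuous: "The five measurements for each examination were averaged for each QUS parameter". CAP, BMI, waist and hip circumference and the laboratory values are continuous too.

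The Sample size section works in cut-off-dependent terms: "Assuming an 80% MAFLD prevalence in the target population and 80% sensitivity and 90% specificity in QUS techniques". The minimum is 75, and "our study will involve 100 patients scheduled to undergo RYGB". The Schedule of the study describes 100 formal and four training cases, and no separate validation set for the main study. The Primary endpoint section counts it a success if QUS evaluates the degree of steatosis better than the other methods, without naming the measure.

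**The concern.** The maximum of an empirical Youden curve picks up chance as well as signal. The chosen cut-off is the one that happened to separate these patients best, so its apparent performance exceeds what it would achieve in new patients. The excess is largest when one class is small. At 80% prevalence the non-steatotic class is only 15 of 75 or 20 of 100.

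Two things are at stake. First, the sensitivities and specificities, which are the quantities the sample size is built on, would be overstated, and the cut-offs would be less reproducible than they look. Second, the amount of overstatement differs between methods, because it depends on how many cut-points can be searched and on how good the marker truly is. A comparison of methods at their own best cut-offs is then not like for like.

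**Working it through.** **Inputs from the article.** Prevalence 80%, sensitivity 80%, specificity 90% and N = 75 or 100 (Sample size). AUC 0.861 for AC-TAI and 0.964 for SC-TSI at PDFF ≥5%, from an earlier study (Discussion). Share with PDFF ≥10% in the pilot: 13/21 = 62% (Results). MAFLD share of more than 95% in one cited series of morbidly obese patients (Introduction).

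**The plan's own figure.** The minimum of 75 cannot be recomputed, because power, the comparator's accuracy and the discordance are not given. The step to 100 fits 25% loss: 75/(1 − 0.25) = 100. The sample sizes are used here only to set class sizes: 0.80 × 75 = 60 against 15, and 0.80 × 100 = 80 against 20.

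**Model (assumed).** The marker is N(0, 1) without steatosis and N(d, 1) with it. Then AUC = Φ(d/√2), and Youden index J = sensitivity + specificity − 1. From 80% and 90%, d = 0.842 + 1.282 = 2.12, AUC = 0.933, and J at that cut-off is 0.80 + 0.90 − 1 = 0.70.

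**Calculation.** In each simulated trial (4,000 or more per setting), find the cut-off with maximum J, record J in that sample (apparent), and compute the true J of the same cut-off from the model. Inflation is apparent minus true.

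| With / without steatosis | AUC | Apparent J | True J at chosen cut-off | Inflation |
|---|---|---|---|---|
| 60 / 15 | 0.861 | 0.643 | 0.530 | 0.113 |
| 60 / 15 | 0.933 | 0.781 | 0.683 | 0.098 |
| 80 / 20 | 0.861 | 0.628 | 0.533 | 0.095 |
| 80 / 20 | 0.933 | 0.770 | 0.689 | 0.081 |

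At AUC 0.964 the inflation is 8.5 points (60/15) and 7.1 points (80/20). Repeat runs differ by a few tenths of a point.

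**Where it falls.** At 60/15 and AUC 0.933, apparent against true sensitivity is 0.882 against 0.863 (about 2 points), and specificity is 0.899 against 0.821 (about 8 points). Percent correctly classified is inflated by only about 3 points, because the overstated specificity applies to one patient in five.

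**Dependence on class balance.** At 62% prevalence the inflation is 7.4 points (N = 75) and 6.3 points (N = 100) at AUC 0.933, and about 5 to 8 points across the AUC range with 100 patients. At 95% prevalence and AUC 0.933 it is 20.6 and 17.8 points.

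**Dependence on marker quality.** At 60/15 the inflation is 15.1 points at AUC 0.65, 13.4 at 0.75, 11.3 at 0.861 and 8.3 at 0.964. Weaker continuous markers gain more.

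**Against a four-grade scale.** Give QUS and a four-grade reading the same true J of 0.71, an assumed correlation of 0.5, and assumed grade boundaries at the optimum and one SD either side. Mean apparent J is then 0.782 against 0.717 at N = 75 (gap 6.5 points) and 0.770 against 0.713 at N = 100 (gap 5.7 points). The gap depends on those boundaries: under different assumed boundaries the four-grade inflation ranged from 0 to about 6 points.

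**Effect of the fix.** At 60/15 and AUC 0.933, a 200-resample bootstrap correction lowers mean J from 0.780 to 0.719, against a true 0.686. It removes (0.780 − 0.719)/(0.780 − 0.686) = 0.061/0.094, about two thirds of the bias.

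**The case against.** The strongest reply is that this is partly a matter of silence. The maximum-Youden cut-off is a conventional descriptive output. The article does not say in words that the resulting sensitivity and specificity go uncorrected, and an analysis plan that is not shown could add a correction. That much stands: scoring on the same patients is an inference. But the selection rule itself is stated, no other main-study sample is described, and the rule followed as written gives biased figures.

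Several stronger readings are tempting, and the documents do not support them:

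- **That accuracy is inflated by 10 points.** The figure is on a sum of two proportions. It is about 2 points of sensitivity, 8 of specificity and 3 of percent correct at N = 75.
- **That the rule favours QUS generally.** It also applies to CAP, BMI and laboratory values, and a weaker continuous comparator gains more than QUS. Only the comparison with B-mode tilts towards QUS.
- **That cut-offs are re-optimised at every visit.** The article does not say whether they are set per visit, before surgery only, or on pooled data. Pooling five visits of 75 as if independent would still leave about 3.6 points.
- **That one class is small at every visit.** The 84% disappearance of steatosis in the Discussion comes from one cited biopsy cohort. It is not a PDFF result and says nothing about 1, 3 or 6 months. Classes may pass through balance after surgery, where inflation is about 6 to 7 points.
- **That the primary conclusion is biased.** The article names no metric for it, and the planned AUC and correlation with MRI-PDFF do not depend on a cut-off.

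**Conclusion.** The point holds in limited form. Cut-offs chosen by the maximum empirical Youden index, with no validation or correction described, will overstate performance read off in the same patients. At 80% prevalence and AUC 0.861 to 0.964 the Youden index is inflated by about 8 to 11 points with 75 evaluable patients and 7 to 10 with 100. Of this, about 6 to 9 points are specificity and about 2 are sensitivity. The inflation is about 5 to 8 points at a 62% share with 100 patients, and much larger if one class is very small.

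These sizes rest on a binormal model with equal variances and on prevalence and AUC values that the article assumes or cites; they are not results of this trial. Comparisons made at these cut-offs are distorted: towards QUS against B-mode, by an amount that rests on assumed grade boundaries, and possibly away from QUS against weaker continuous markers. The distortion matters for the superiority claim only if sensitivity, specificity or the Youden index is used to decide it.

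**What to change.** For every method and for both PDFF thresholds, report sensitivity, specificity and Youden index with bootstrap optimism correction, or cross-validated. Resample patients rather than single examinations, and repeat the cut-off search inside each resample. Label any uncorrected value as apparent.

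Base the comparison between methods on paired AUC differences with confidence intervals, which need no cut-off and build on ROC curves already planned. State also whether cut-offs are set per visit, before surgery or on pooled data. Carrying pre-operative cut-offs forward unchanged is not an obvious default, because the Discussion itself warns that subcutaneous fat may influence QUS values.

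The cost is a few lines of R and no extra patients or visits. Reported accuracy becomes somewhat less favourable, and the correction removes most but not all of the bias.

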## Results

Prior to the fomal study, we recruited 21 Chinese participants who satisfied: (1) age between 18 and 85 years old; (2) with suspected NAFLD, and (3) agreed to receive QUS, and MRI examination. They received ultrasonic examination (TAI, TSI, CAP) and MRI-PDFF (Figure 3).

**Figure 3 F3:**
[figure not shown]
Quantitative analysis of liver fat in an obese Chinese male. Based on B-mode ultrasound image, the color-coded maps of TAI map (**A**) reflecting center frequency and TSI map (**B**) reflecting Nakagamia parameters are generated. (**C**) MRI-PDFF values were 14.72%.

The average BMI of all participants was 26.43, which meets the diagnostic criteria for overweight. More than 50% of patients (15/21, 71.43%) presented with symptom of right upper abdominal distension. For the value of MRI-PDFF, the average was 13.86%. MRI results from eight patients were below 10%. For MRI-PDFF ≥10%, a total of 13 patients were in this category (13, 62.9%).

All the data were analyzed in R (v4.3.1; R Core Team). A two-sided *P* < 0.05 was considered statistically significant. AC-TAI showed moderate correlations with MRI-PDFF (adjusted *r* = 0.632; *P* < 0.05). Linear correlation between SC-TSI and MRI-PDFF was not significant (*P* = 0.982) (Table 1). For MRI-PDFF ≥10%, SC-TSI showed moderate correlations with MRI-PDFF (adjusted *r* = 0.677; *P* < 0.05) (Figure 4). In a way, the results signified the feasibility of using QUS techniques for postoperative evaluation of bariatric surgery.

**Table 1 T1:** Linear regression between AC-TAI/SC-TSI and other parameters.

Parameters	AC-TAI		SC-TSI	
	Adjusted R	*P*-value	Adjusted R	*P*-value
CAP	0.578	<0.05	0.343	0.070
MRI-PDFF	0.632	<0.05	0.229	0.982

**Figure 4 F4:**
[figure not shown]
Scatterplot of SC-TSI and MRI-PDFF.

## Discussion

The rising prevalence of obesity has emerged as a significant public health challenge across the world, affecting both developed and developing nations. Among the numerous adverse consequences of obesity, an important correlation has been established between its degree and the incidence and severity of MAFLD. In fact, obesity has been found to increase the likelihood of developing MAFLD by 4.6 times (22). The natural course of MAFLD indicates that fibrosis manifests in around 32–37% of patients within 3–6 years, and approximately 12% of patients tend to progress to cirrhosis over 8–10 years (23).

Therapeutic interventions such as bariatric surgery have demonstrated potential in ameliorating steatosis, hepatic fibrosis, and necroinflammatory activity, especially for those with morbid obesity and NASH. Weiner et al. (24) conducted a study to evaluate the impact of bariatric surgery on the histological development of NASH. They discovered, through liver biopsy results, that 82.8% of patients exhibited complete regression of MAFLD. Dixon et al. (25) investigated the outcomes of weight loss following Roux-en-Y gastric bypass (RYGB) on liver histology and plasma aminotransferase levels (AST, ALT, and GGT) in 60 severely obese individuals. Results indicated that the mean weight loss was 31.5 ± 18 kg, and there was notable improvement in AST, ALT, GGT, lobular steatosis, inflammation, and fibrosis. Furuya et al. (26) enrolled a cohort of MAFLD patients undergoing RNYGB, and procured a wedge liver biopsy during the operation. The initial evaluation revealed that 67% of the patients had NASH, while 33% had steatosis, and cirrhosis was present in 5.5% of those with NASH. Following an average excess weight loss of 60%, steatosis and fibrosis disappeared in 84% and 75% of the patients respectively.

Continuous surveillance of hepatic steatosis following bariatric surgery is crucial for effective disease management and prompt therapeutic intervention, ultimately leading to improved health outcomes and reduced healthcare costs (10). Recently, several QUS approaches have emerged for the quantification of hepatic steatosis. The advantages of a US-based hepatic fat quantification system are numerous, including widespread availability, real-time functionality, and low cost. Recent studies have demonstrated that certain quantitative parameters derived from RF data analysis, which reflect the backscatter or attenuation of US beams, exhibit strong correlation with hepatic steatosis grades (27–29). Jeon et al. (30) investigated the diagnostic potential of QUS parameters in assessing hepatic steatosis among MAFLD patients, using MRI-PDFF as the reference standard. They found that both AC-TAI and SC-TSI were significantly correlated with MRI-PDFF (*r* = 0.659 and 0.727, respectively). For detecting hepatic fat contents ≥ 5%, the areas under the receiver operating characteristic (ROC) curves of AC-TAI and SC-TSI were 0.861 and 0.964, respectively. Bae et al. (31) on the other hand, evaluated the diagnostic performance of the normalized local variance ultrasound technique in detecting fatty liver, using histopathology as a reference standard. The areas under the ROC curve for detecting fatty livers of varying degrees were 0.911 for ≥S1, 0.974 for ≥S2, and 0.954 for ≥S3. This study aims to provide evidence supporting the feasibility of utilizing QUS techniques for liver fat quantification. Furthermore, we aim to prospectively evaluate the application value of QUS techniques in quantitatively assessing hepatic steatosis after bariatric surgery (32, 33).

Pereira et al. (34) conducted a comparison of noninvasive biochemical methods and FibroScan with histopathologic analysis to evaluate hepatic fibrosis in patients who underwent bariatric surgery one year prior. The results indicate that noninvasive liver fibrosis evaluation correlates highly with liver biopsy findings after one year of bariatric surgery. While QUS techniques (TAI, TSI) are more advanced ultrasound technologies, they can theoretically assess the degree of hepatic steatosis accurately after bariatric surgery. In our pre-experiment study, we preliminarily verified the feasibility of the QUS techniques in Chinese participants who suspected NAFLD. The results of the pre-experiment signified the feasibility of using QUS techniques for postoperative evaluation of bariatric surgery, making our study design reasonable.

Our study inevitably has some limitations. Specifically, we utilized MRI-PDFF rather than biopsy as the gold standard to correlate QUS parameters. Although previous research suggests that MRI-PDFF exhibits relatively high sensitivity and specificity in detecting fatty liver disease, there remains potential for incorrect diagnoses. In addition, although we conducted health education for participants before surgery, it was difficult to avoid that confounding factors (like life-style) may influence on results. Furthermore, confounding factors such as increased subcutaneous fat in individuals with higher BMI may influence QUS parameter results. With a larger patient population, we will summarize the imaging experience in hepatic steatosis evaluation by QUS techniques in obese people. We will also analyze the influence of scanning methods, imaging location and other influencing factors on the results, and explore how to improve the results.

## Conclusion

In conclusion, this article has described methods for using QUS techniques (TAI, TSI) to assess hepatic steatosis and its changes in obese individuals before and after bariatric surgery. In addition, we compare QUS techniques to anthropometric measurements, laboratory assessments and other imaging methods. By this study, QUS techniques will be signed a widespread availability, real-time functionality, and low cost approach for assessing hepatic steatosis before and after bariatric surgery in obese individuals. Our pre-experiment results signified that using QUS techniques for postoperative evaluation of bariatric surgery is promising. Our study is the first one in China to investigate the application value of QUS techniques (TAI, TSI) in quantitatively assessing hepatic steatosis after bariatric surgery. Our study will provide strong evidence regarding whether obese people can truly benefit from QUS techniques in liver fat quantification.

## Data Availability

The original contributions presented in the study are included in the article/Supplementary Material, further inquiries can be directed to the corresponding authors.
